### Secondary outcomes

2.5

Secondary outcomes will include the pain-free interval (defined as the time from the end of surgery to the first onset of pain), resting and cough-evoked pain Visual Analog Scale (VAS) scores (ranging from 0, no pain, to 10, worst imaginable pain) assessed at 6, 12, 24, 48, and 72 h postoperatively; maximum pain scores at 24, 48, and 72 h; intraoperative and total postoperative opioid consumption; time from the end of surgery to first request for rescue analgesia and the number of such requests; anxiety and sleep quality (using numeric rating scores, NRS, 0–10, higher indicating greater anxiety/ greater sleep) at 24, 48, and 72 h; patient satisfaction with analgesia measured using an NRS (0–10, higher indicating greater satisfaction); incidence and severity of postoperative nausea and vomiting (PONV), graded on a 4-point scale (0 = none, 1 = nausea only, 2 = 1–3 vomiting episodes, 3 = ≥4 episodes) and the number of rescue antiemetic administrations at 24, 48, and 72 h; as well as patient confidence in coughing and ambulation, both assessed using an NRS (0 = no confidence to 10 = full confidence). All postoperative assessments will be performed daily at 17:00 until 3 days after surgery. The following outcomes will be recorded prior to patient discharge: the incidence of pneumothorax or hemothorax during the entire postoperative period, total postoperative drainage volume, and length of hospital stay.

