### Randomization and blinding

2.7

This open-label, three-arm randomized trial will assign 162 participants in a 1:1:1 ratio (Group L, Group R, and Group P, with 54 participants per group). An open-label design will be adopted due to fundamental differences in postoperative pain management protocols among the three groups. To facilitate protocol-adherent adjustments in analgesia, both investigators and participants will not be blinded to treatment allocation. Nevertheless, postoperative outcome assessments will be performed by trained nurses who are not involved in the intervention procedures to minimize potential bias.

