### Statistical analysis

2.11

The normality of continuous variables will be assessed using the Shapiro–Wilk test. Data following a normal distribution will be reported as mean (standard deviation, SD), while non-normally distributed data will be presented as median (interquartile range, IQR). Binomial variables will be expressed as proportions. The correlation structure will be selected based on the quasi-likelihood under the independence model criterion (QIC). Data distribution will determine the use of either a normal or gamma distribution with identity or log-link functions. The primary hypothesis of this study is that group L can demonstrate a superior quality of postoperative recovery compared to both control groups, with the difference being both statistically and clinically significant. A generalized estimating equation (GEE) model will be used to analyze repeated measures of continuous variables accounting for within-subject correlations. Continuous variables measured at a single time point will be analyzed using *t*-tests or Mann–Whitney U tests depending on normality and categorical data will be analyzed using the χ^2^ test. Post-hoc pairwise comparisons are strictly contingent on a significant overall between-group difference and *p*-values are adjusted using the Bonferroni method and set at 0.017. For longitudinal outcomes, this correction governs testing at both the individual time-point and overall treatment effect levels, ensuring robust control of the type I error rate. Statistical significance will be defined as *p* < 0.05.

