## Discussion

3

This prospective, open-label, randomized controlled trial plans to enroll 162 adult patients at our center. It is designed to evaluate the effect of a single ultrasound-guided paravertebral block using liposomal bupivacaine on postoperative recovery quality compared to conventional opioid-dependent intravenous analgesia and an established high-quality multimodal analgesia protocol. The trial will be conducted in accordance with the Consolidated Standards of Reporting Trials (CONSORT) guidelines. In addition to assessing overall recovery quality, the study will address three key clinical questions: whether the intervention provides sufficient baseline analgesia; whether it independently meets current standards for comprehensive pain management; and whether it confers significant clinical benefits beyond analgesia. The primary outcome is the overall quality of recovery, as measured by QoR-15 score at 24, 48, and 72 h after surgery. Secondary outcomes include multiple pain management quality assessments (such as pain-free interval and pain scores under various conditions), total consumption of sufentanil during surgery and hospitalization, anxiety and sleep quality scores at 24, 48, and 72 h postoperatively, the incidence and severity of PONV along with the use of rescue antiemetics at the same intervals, and patient confidence in coughing and ambulation assessed using an NRS. All postoperative evaluations will be performed daily at 17:00 until 3 days after surgery. Additional recorded outcomes include the incidence of pneumothorax or hemothorax, total postoperative drainage volume, and length of hospital stay.

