As recommended by clinical guidelines (24, 31, 32), postoperative analgesia should follow an opioid-sparing strategy, which is also a key advantage of multimodal analgesia. This approach not only improves the quality of pain control but also reduces opioid-related adverse effects. The aim of this prospective randomized controlled trial is to combine paravertebral block (PVB) technique with liposomal bupivacaine to investigate the impact of a single-injection ultrasound-guided PVB using liposomal bupivacaine on the quality of postoperative recovery. No placebo control for the purpose of balancing interventions will be included, so as to directly reflect the true clinical effect and value of this strategy. Furthermore, among the secondary outcomes, we plan to specifically analyze the postoperative analgesic quality of this strategy and its contribution to reducing adverse effects such as nausea and vomiting, thereby comprehensively evaluating the clinical significance of this catheter-free and opioid-sparing postoperative pain management approach. By comparing with two reference groups—patients receiving PCIA alone and those receiving PCIA combined with ropivacaine-based PVB—this study will assess the extent of improvement in postoperative recovery quality achievable with ultrasound-guided single-injection PVB using liposomal bupivacaine. Our hypothesis posits that a catheter- and opioid-free pain management strategy—enabled by the sustained-release profile of liposomal bupivacaine and high-precision ultrasound-guided thoracic paravertebral blockade—can provide effective analgesia after thoracic surgery. This RCT will help advance the transformation of pain management paradigms in real-world clinical practice.

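### PONV severity, four ordered grades at three times, is sent to a chi-square test that uses neither the order nor the three times jointly: valid at one time, but inefficient if treatment shifts all grades

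*Protocol article*

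**What the plan says.** All references are to the protocol article.

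- **Outcome (section 2.5).** PONV severity is "graded on a 4-point scale (0 = none, 1 = nausea only, 2 = 1–3 vomiting episodes, 3 = ≥4 episodes"). It is a secondary outcome, listed with PONV incidence and rescue antiemetic use.
- **Timing (Table 1 and section 3).** Table 1 marks both incidence and severity at 24, 48 and 72 h. The Discussion again lists "the incidence and severity of PONV along with the use of rescue antiemetics at the same intervals".
- **Repeated measures (section 2.11).** "A generalized estimating equation (GEE) model will be used to analyze repeated measures of continuous variables accounting for within-subject correlations". For the model's distribution: "Data distribution will determine the use of either a normal or gamma distribution with identity or log-link functions". No binomial or ordinal form is named.
- **Categorical data (section 2.11).** "categorical data will be analyzed using the" chi-square test. No exception is made for ordered or repeated categories.
- **Effect measures (section 2.11).** Odds ratios with 95% confidence intervals are promised where appropriate, but no model is named that would produce them.
- **Role in the argument (section 3).** The trial intends to examine specifically the strategy's analgesic quality and "its contribution to reducing adverse effects such as nausea and vomiting".

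**The concern.** The grades have a clear direction, and the question asked of them is directional: is PONV less severe in group L? Pearson's chi-square treats the four grades as unordered labels. In the three-arm table it spreads the comparison over (3 − 1) × (4 − 1) = 6 degrees of freedom, whereas a test using the order needs 3 − 1 = 2.

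The three times are a second problem. Section 2.11 says its Bonferroni correction applies to longitudinal outcomes both at individual times and for the overall treatment effect, but no method named there gives an overall effect for PONV severity. Chi-square at each time gives three separate answers. Chi-square on pooled patient-days would treat repeated observations of one patient as independent. The text does not say which is meant.

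At stake is how sharply the trial can answer one of its secondary questions, and whether it reports an interpretable effect size for it.

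**Working it through.** **1. Plan's own figure.** None exists for this outcome. The sample size in section 2.10 concerns the QoR-15 only, and no grade distribution, effect size or power for PONV is stated.

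**2. Inputs from the article.** Three arms of 54 ("Group L, Group R, and Group P, with 54 participants per group"), four grades, overall two-sided level 0.05, pairwise level 0.017.

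**3. Inputs assumed.** Control grades (none / nausea only / 1–3 episodes / 4 or more) of 50/25/17/8%, and as alternatives 45/25/20/10%, 40/30/20/10%, 60/20/15/5% and 75/15/8/2%. The common odds ratio for a lower grade in group L runs from 1.5 to 4.

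**4. Formula.** If C is the control probability of being at or below a grade, group L has odds OR × C/(1 − C). With 50/25/17/8% and OR = 2.5:
- C = 0.50: odds 1 × 2.5 = 2.5, probability 2.5/3.5 = 0.714.
- C = 0.75: odds 3 × 2.5 = 7.5, probability 7.5/8.5 = 0.882.
- C = 0.92: odds 11.5 × 2.5 = 28.75, probability 28.75/29.75 = 0.966.

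Group L grades are therefore 71.4/16.8/8.4/3.4%.

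**5. Power at one time, order ignored or used.** Simulated trials compared Pearson chi-square with the tie-corrected rank test (Kruskal–Wallis for three arms, Mann–Whitney for two).

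| Scenario | Chi-square | Rank test | Gap (points) |
|---|---|---|---|
| 50/25/17/8, OR 2.5, three arms, R = P, 0.05 | 48% | 69% | 21 |
| Same, L vs P, 0.0167 | 30% | 49% | 19 |
| 45/25/20/10, OR 2, L vs P, 0.05 | 31% | 47% | 16 |
| 45/25/20/10, OR 3, L vs P, 0.05 | 66% | 82% | 16 |
| 75/15/8/2, OR 1.5, L vs P, 0.017 (smallest gap) | 2.7% | 6.1% | 3 |
| 75/15/8/2, OR 4, three arms, R = P, 0.05 (largest gap) | 45% | 70% | 25 |

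Repeat runs of the first two rows agree within two points.

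**6. Validity.** With no treatment effect, the two-arm chi-square at one time rejected in 3.7% to 4.8% of simulated trials at a nominal 5%.

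**7. Effects that are not a common shift.** L versus P at 0.05, control 45/25/20/10%:

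| Group L grades | Chi-square | Rank test |
|---|---|---|
| 45/45/8/2 | 71% | 20% |
| 60/10/20/10 | 41% | 18% |
| 55/35/8/2 | 60% | 44% |

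Chi-square is the stronger test in all three patterns.

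**8. Using the three times as well (indicative only).** A rank test on the grade summed over three days was compared with chi-square at one time. The odds ratio was the same each day, and the latent within-patient correlation was 0.36 (borrowed from the QoR-15) or 0.6. For 45/25/20/10% and OR 2, power rises from about 31% to 72% or 63%. Over OR 1.5 to 3 the gap is about 12 to 50 points at 0.05. This shows that the repeated data carry information. It is not the power of the GEE proposed below, which was not simulated.

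**The case against.** - **The chi-square clause may cover single-occasion data only.** It shares a sentence with a clause on continuous variables measured once. Entering the 0–3 grade as a score in the GEE is not expressly excluded, and the article does not say that all categorical data go to chi-square. This softens the point but does not remove it. The single-occasion qualifier is attached to the continuous variables, the GEE sentence is limited to continuous variables, and no other method is named for repeated categories.
- **This is detail for an analysis plan.** That holds for a fallback to an exact test when cells are sparse, and no point is made of it. In the scenario with control grades of 50/25/17/8%, some expected count falls below 5 in most simulated tables, but this produced no demonstrated error. The choice of test differs, because the article names one.
- **Odds ratios are promised.** They are, but a 3 × 4 chi-square does not yield one for the severity grade, and no model is named that would.
- **PONV is also measured by incidence and rescue antiemetic use.** This stands. For incidence at one time there is no order to lose and chi-square is standard. The loss from ignoring order concerns severity alone.
- **The power loss depends on the scenario.** This stands. A reader might infer that the plan as such gives up 20 points. The article does not support that: it gives no PONV rates or effect size, the gap varies widely under a shift, and step 7 shows it can reverse.

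**Conclusion.** The point holds as a minor one. Read as written, section 2.11 analyses an ordered outcome, measured three times, with a test that ignores the order, and gives no joint analysis of the times. The single-time test keeps its error rate; what is lost is efficiency and a single effect estimate.

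The loss from ignoring order is roughly 3 to 25 points of power at one time. This assumes 54 per arm, the control distributions listed and a common odds ratio of 1.5 to 4. A figure near 20 points belongs to particular scenarios, such as 50/25/17/8% with an odds ratio of 2.5. If treatment mainly moved patients from vomiting to nausea alone, leaving incidence unchanged, chi-square could be the better test.

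Nothing here bears on the QoR-15 analysis, the sample size or the primary conclusion, and nothing shows the chi-square results at one time to be invalid.

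**What to change.** Change the wording of section 2.11 before the data are analysed:

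- **PONV severity:** a cumulative-logit (proportional-odds) GEE over 24, 48 and 72 h with group, time and group-by-time, reporting the common odds ratio with its 95% CI. This also supplies the model behind the odds ratios that the section mentions.
- **PONV incidence:** a binary-logit GEE over the same three times.
- **Categorical outcomes recorded once:** keep the chi-square test.

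The cost is a few sentences and slightly more analysis, with no change to data collection or sample size. There is a small downside: the proportional-odds assumption needs a check, and power is lower if the effect is not a shift across grades. Tabulating the grades by arm and time would let readers see such a pattern.

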### Sample size calculation

2.10

The primary outcome will be the QoR-15 score, evaluated at 24, 48, and 72 h after surgery. Based on previously published data, the minimal clinically important difference (MCID) for the QoR-15 is set at 8 points (22), with an estimated standard deviation (SD) of 12 (23). Using an independent-sample *t*-test calculation with a two-sided alpha of 0.05 and 80% power (beta = 0.2), an initial sample size of 36 patients per group will be estimated to detect a statistically significant difference in mean QoR-15 scores. However, because the trial involves three groups and planned pairwise comparisons, a Bonferroni correction will be applied, adjusting the significance threshold to 0.017 (0.05/3). Additionally, since the primary outcome entails repeated measures over three time points, the sample size will be adjusted using an intraclass correlation coefficient (ICC) of 0.36, derived from pilot data. After these adjustments, a minimum of 48 participants per group will be required. The final sample size was calculated using the following formula for repeated measures: The formula is 
$n=\frac{{\left(Z_{1-a/2}+Z_{1-\beta }\right)}^{2}\times (1+(\kappa -1)\rho )\times \sigma^{2}}{\Delta^{2}\times (1-\rho )}$

*n* is the sample size required per group, 
κ
 is the number of repeated measurements (3 in this study), 
σ
 is the standard deviation (12), 
Δ
 is the minimal clinically important difference (8), and 
σ
 is the intraclass correlation coefficient (0.36). This number will then be inflated by 10% to account for potential attrition, loss to follow-up, or major missing data, resulting in a final sample size of 54 patients per group. Thus, a total of 162 patients (54 per group) will be enrolled.

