All study outcomes will be analyzed in the modified intentiontotreat (mITT) population, including all patients who are randomized, received the assigned intervention, and completed all or part of the postoperative follow-up assessments. Patients will be included in the analysis according to their original allocation. To evaluate the robustness of the primary outcome and its sensitivity to protocol deviations, a per-protocol (PP) analysis will be performed as a sensitivity analysis to verify the reliability of the findings from the intention-to-treat analysis. Multiple testing correction will be applied to primary and secondary outcome measures where applicable. As a theoretical principle, this adjustment is generally not applied to safety indicators. Odds ratios (OR) and corresponding 95% confidence intervals (CI) will be reported where appropriate. No interim analysis will be planned. Missing data will not be imputed. Statistical analyses will be performed using SPSS (version 25.0; IBM SPSS). A two-sided *p*-value < 0.05 will indicate statistical significance, except where false discovery rate (FDR) corrections apply.

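### One Bonferroni threshold for three group pairs is reused at every time point, so the stated type I error control fails for the day-by-day QoR-15 comparisons; the adjustment and FDR wording is also unresolved

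*Protocol article*

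**What the plan says.** The Sample size calculation section (2.10) derives the pairwise threshold: "a Bonferroni correction will be applied, adjusting the significance threshold to 0.017 (0.05/3"). It is justified there by three groups and their pairwise comparisons; the three time points play no part in it.

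The Statistical analysis section (2.11) makes four statements that bear on significance:

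- Pairwise comparisons follow only if the overall group difference is significant. Of the resulting p-values, the section says that they "are adjusted using the Bonferroni method and set at 0.017".
- On outcomes measured repeatedly, it adds that "this correction governs testing at both the individual time-point and overall treatment effect levels, ensuring robust control of the type I error rate".
- A general rule comes next, with a cut-off of 0.05: "Statistical significance will be defined as" a p-value under that level.
- The 0.05 rule is repeated at the end of the section, "except where false discovery rate (FDR) corrections apply". No FDR procedure is described and no outcome is assigned to one.

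The same section states the primary hypothesis as superiority of group L over both control groups. QoR-15 is measured at 24, 48 and 72 h.

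**The concern.** The division 0.05/3 allows for three pairs compared once. Section 2.11 uses the same 0.017 for each pair at each of three days and again for the overall effect, and then claims robust error control at both levels. Nothing in the threshold pays for the extra tests.

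Two pieces of wording add to this. Adjusting p-values by Bonferroni and lowering the cut-off to 0.017 are alternative forms of the same correction; a sentence that names both can be carried out as a double correction. An FDR exception beside a Bonferroni rule, with no outcomes named, leaves open which error criterion applies where.

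What is at stake is mainly the credibility of single-day claims, such as a difference at 72 h, and the freedom to choose after the data are seen. A raw pairwise p of 0.01 passes at 0.017 and fails under a double correction. In an open-label trial with a patient-reported primary outcome, that choice should be closed beforehand.

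**Working it through.** **Inputs.** From section 2.10: difference 8, SD 12, ICC 0.36, three time points, two-sided alpha 0.05, 48 per group before attrition and 54 enrolled. Assumed, because not stated: the overall gate is tested at 0.05, correlation is exchangeable, and simple contrasts of means stand in for the GEE contrasts.

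**The plan's own figure.** 0.05/3 = 0.0167, printed as 0.017. It is reproduced.

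**Count of tests.** 3 pairs × (3 days + overall) = 12. Bonferroni sums at 0.0167: three pairs once, 3 × 0.0167 = 0.05; nine day-level tests, 0.15; all 12, 0.20. If the tests were independent, the chance of at least one false claim would be 1 − (1 − 0.0167)^9 = 0.140, or 0.183 for 12.

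**Simulation, 48 per group, 200,000 replicates.** Chance of at least one false claim among those of the 12 tests whose null is true:

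| True state | Group main-effect gate | Joint group and group-by-time gate (6 df) |
|---|---|---|
| L +8 at 24 h only | 5.8% | 9.9% |
| L +16 at 24 h only | 7.9% | 10.0% |
| L +16 and R +8 at 24 h only | 5.8% | 8.3% |

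Under the complete null, either gate gives about 4 to 5%; with no gate the rate is 12.7%.

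A separate run with 54 per group and t-tests (40,000 replicates) agrees. Under the complete null it gives 4.6% with one overall gate, 12.0% with a separate gate per time point, and 13.1% with no gate. With one gate and an effect at 24 h only it gives 6.1% (+8) and 8.2% (+16); at correlation 0.6 these become 5.7% and 6.9%. With L +8 at all three days and R = P it gives 5.2%.

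**Why the gate does not rescue the claim.** With L better at 24 h only, eight of the 12 nulls are still true: three pairs at 48 h, three at 72 h, and R–P at 24 h and overall. Once the real effect opens the gate, those eight tests share a Bonferroni sum of 8 × 0.0167 = 0.133.

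**The primary claim.** Take the worst case: L = R, P far worse, the gate always open, and success on L–R allowed on the overall contrast or any day. At least one L–R rejection occurs about 5% of the time two-sided, and about 2.5% in favour of L. The claim that L beats both therefore stays within 5%.

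**The double-correction reading.** If a p-value is multiplied by 3 and then compared with 0.05/3, the raw threshold is 0.05/9 = 0.0056 (critical z 2.773 instead of 2.394).

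- One day: z = 8/(12 × √(2/48)) = 3.266. Power per pair is Φ(3.266 − 2.394) = 81%, falling to Φ(3.266 − 2.773) = 69%.
- Mean of three days: the variance factor is (1 + 2 × 0.36)/3 = 0.573, so z = 3.266/√0.573 = 4.313. Power is Φ(1.919) = 97%, falling to Φ(1.540) = 94%.

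**The case against.** The strongest reply is that the trial's hypothesis is a conjunction, and that counting any false rejection among 12 tests, R–P included, measures something wider than that hypothesis. This stands. A reader might infer that the primary claim itself carries an error of 8 to 13%; the worst-case check does not support that.

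The gate also matters. It is stated, so the ungated 13% should not be presented as the plan's error rate. One overall gate controls the complete null, and the excess under partial nulls is moderate. What remains is that section 2.11 does not say whether the gate is one test or one per time point, and that choice moves the complete-null rate from about 4–5% to about 12%.

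Three stronger readings are tempting and not supported:

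- That 0.05 and 0.017 contradict each other. They can coexist: 0.05 for the overall test, 0.017 for raw pairwise p-values.
- That the plan does correct twice. Section 2.10 speaks of adjusting the threshold, so the sentence in 2.11 may be only loose wording. A double correction would also be conservative, so it could not explain a loss of error control.
- That the gate cannot be run for single-time outcomes because only two-sample tests follow "Continuous variables measured at a single time point will be analyzed using". Naming a three-group test is detail that a condensed article may leave to the analysis plan.

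What the objection does not meet is that the article asserts error control at the time-point level, which its threshold does not deliver, and that the FDR clause has no stated scope.

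**Conclusion.** The point holds for the day-by-day family. Strong control of type I error is claimed and not delivered: about 6 to 8% or 8 to 10%, depending on the form of the gate, when the effect is limited to 24 h, and about 12 to 13% under the complete null if the gate is run per day or omitted. Under the complete null with one overall gate, the error is controlled.

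These sizes rest on the protocol's SD and ICC, an assumed 0.05 gate, and contrasts of means in place of GEE. The early-only effects of 8 and 16 points are chosen for illustration; a sustained effect of 8 points gives close to 5%.

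The primary conjunctive claim is not inflated, but its deciding contrast is not fixed. The double correction is a possible reading with a modest cost for the averaged contrast. The unassigned FDR exception conflicts with the Bonferroni rule as written. This should be fixed; it does not undermine the design.

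**What to change.** Reword section 2.11 as follows.

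1. The deciding primary tests are the GEE contrasts averaged over 24, 48 and 72 h for L–R and L–P; success requires both.
2. Keep 0.05 for the overall test, and state that it is a single test. For pairwise tests, compare the raw p-value with 0.0167 or the Bonferroni-adjusted p-value with 0.05, never both.
3. Either treat day-by-day contrasts as descriptive, or test a pair's days only after that pair's overall contrast is significant, with correction across the three days. Each pair then spends at most 0.0167, and three pairs at most 0.05. If neither is adopted, delete the error-control claim for the time-point level.
4. Remove the FDR clause, or tie it to named secondary outcomes.

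In the 54-per-group simulation, 0.05/3 used for the overall contrasts only, behind the gate, gives a familywise error of at most 4.1%. A threshold of 0.05/9 over the nine day-level tests gives 4.4% under the complete null and 1.5 to 3.5% under partial nulls.

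The cost is rewording, with no change to design, data or sample size, and somewhat less power for single-day claims: at 0.05/9, 69% instead of 81% per pair for an 8-point difference.

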### Exclusion criteria

2.3

Exclusion criteria will include:

Known allergy to local anesthetics, nonsteroidal anti-inflammatory drugs, or opioids;Preexisting chronic pain of thoracic or back origin;Contraindications to regional puncture such as coagulopathy, local infection or inflammation;Psychiatric disorders;History of ipsilateral thoracotomy;Referral for thoracotomy;History of chronic opioid use or substance abuse;Bilateral surgery.

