### Anesthetic and study interventions

2.8

All patients will fast for at least 8 h and refrain from clear fluids for at least 4 h prior to surgery. In the operating room, following the establishment of peripheral intravenous access, patients will receive oxygen via face mask at 5 L/min and undergo continuous monitoring of vital signs, including non-invasive blood pressure, percutaneous arterial oxygen saturation (SpO₂), heart rate, respiratory rate, and bispectral index (BIS). Under aseptic conditions, a radial arterial catheter will be inserted for continuous invasive arterial pressure monitoring. Anesthesia induction will be performed using propofol (2 mg/kg), sufentanil (0.5 μg/kg), and rocuronium (0.6 mg/kg). After induction of anesthesia, adequate topical anesthesia of the larynx and upper trachea will be achieved using lidocaine. Following preoxygenation, a double-lumen endobronchial tube will be placed. Correct positioning and depth of the double-lumen tube will be confirmed before initiating mechanical ventilation. The patient will then be repositioned into the lateral decubitus position with the surgical side uppermost.

A single senior anesthesiologist will perform ultrasound-guided thoracic paravertebral blocks under sterile conditions for all patients in groups L and R. The target injection levels are T4 and T6. For group L, under real-time ultrasound guidance and after confirming correct needle tip position, 10 mL of liposomal bupivacaine (133 mg/20 mL) (21) will be injected at each of the T4 and T6 levels according to a standardized technique, for a total volume of 20 mL. For group R, under identical ultrasound-guided and aseptic conditions, 10 mL of ropivacaine (0.5%) will be injected at each of the T4 and T6 levels, for a total of 20 mL. Patients in group P will not receive any nerve block. Following surgery, patient-controlled intravenous analgesia (PCIA) will be prepared for patients in groups R and P, but not for those in group L. Each PCIA pump will be prepared with a total volume of 100 mL, containing sufentanil and 8 mg of ondansetron. The total sufentanil dose will be calculated as 2 μg per kilogram of body weight. The background infusion will be set at a rate of 0.04 μg/kg/h. Additionally, the PCIA protocol will be configured with a bolus dose of 0.04 μg/kg and a lockout interval of 15 min to ensure medication safety.

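### The primary analysis set leaves out randomized patients who did not receive their assigned intervention, and the only sensitivity analysis cannot show whether this matters

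*Protocol article*

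**What the plan says.** Section 2.11 (Statistical analysis) fixes one population for everything: "All study outcomes will be analyzed in the modified intentiontotreat (mITT) population". It defines that population as "including all patients who are randomized, received the assigned intervention, and completed all or part of the postoperative follow-up assessments". It then adds: "Patients will be included in the analysis according to their original allocation".

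The one sensitivity analysis is per-protocol. Its stated purpose is "to verify the reliability of the findings from the intention-to-treat analysis". No intention-to-treat set is defined anywhere in the article. On incomplete data the section says: "Missing data will not be imputed".

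Three other places bear on who can fail the receipt condition:

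- **Section 2.8 (Anesthetic and study interventions).** One senior anesthesiologist performs "ultrasound-guided thoracic paravertebral blocks under sterile conditions for all patients in groups L and R". Group P has no block. PCIA is prepared after surgery for R and P, not for L.
- **Section 2.9, Table 1.** Randomization falls on the day before surgery; the interventions are marked as intraoperative.
- **Section 2.7 (Randomization and blinding).** Neither investigators nor participants are blinded.

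**The concern.** Randomization makes the arms comparable on the day of allocation. A set that then asks whether each patient received the assigned treatment selects on something that happens later. That is harmless only if non-receipt is unrelated to arm or unrelated to outcome, and here neither can be taken for granted. There is a day between allocation and treatment, the arm is known to the people delivering care, and what counts as receipt differs by arm. Reasons for not giving a component, such as difficult anatomy or an unstable patient, may also predict a poor recovery score.

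The sentence on original allocation does not help. It governs how patients already in the set are grouped and cannot bring back one who was removed for non-receipt. A crossover, for example, fails the receipt condition before the grouping rule applies.

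At stake is the primary hypothesis in Section 2.11, that L is superior to both controls. If non-receipt turned out to be more than rare, the planned analyses could not show how far the result depended on the exclusion.

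**Working it through.** **Inputs from the document.** 54 patients per arm (Sections 2.7 and 2.10). Minimal clinically important difference 8 points, SD 12, two-sided alpha 0.05, 80% power, pairwise threshold 0.05/3, 10% inflation (Section 2.10).

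**The plan's own figures.** With n = 2(z₁₋α/₂ + z₁₋β)² × 12² / 8²:

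- alpha 0.05: 35.3, so 36 per group, as stated;
- alpha 0.05/3: 47.1, so 48, as stated;
- 48 / 0.90 = 53.3, so 54, as stated.

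The 48 is matched here by the Bonferroni adjustment alone. The printed repeated-measures formula with both adjustments gives about 63, which is a separate matter on which this point does not rest. What matters here is that the 10% is described as covering attrition, loss to follow-up and major missing data. Non-receipt is not named, and no rate for it is given.

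**Who can fail the receipt condition** (Section 2.8 read with Section 2.11):

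| Arm | Assigned components | Ways to fail |
|---|---|---|
| L | block | block not given |
| R | block and PCIA | block not given, or PCIA not given |
| P | PCIA | PCIA not given |

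All three arms are exposed, but to different events at different times.

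**Size of the shift.** Let a share f of one arm be excluded, and let those patients score d points below the patients retained, whose mean is m. The as-allocated mean is (1 − f)m + f(m − d) = m − f·d. The retained mean is m, so exclusion raises the arm mean by f·d. Both f and d are assumptions. With 54 per arm, f = 2%, 5% and 10% is about 1, 3 and 5 patients.

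| f | d = 5 | d = 10 | d = 15 | d = 20 | d = 30 |
|---|---|---|---|---|---|
| 2% | 0.10 | 0.20 | 0.30 | 0.40 | 0.60 |
| 5% | 0.25 | 0.50 | 0.75 | 1.00 | 1.50 |
| 10% | 0.50 | 1.00 | 1.50 | 2.00 | 3.00 |

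The range is 0.1 to 3.0 points, that is 0.1/8 = 1% to 3.0/8 = 38% of the 8-point difference. The upper end needs a deficit of 30/12 = 2.5 planning SDs, which is extreme.

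**From arm mean to comparison.** The bias in a difference is f₁d₁ − f₂d₂. With 5% and 20 points in both L and R, the shift in L versus R is 1.0 − 1.0 = 0. With 5% in L and 2% in P at the same deficit, it is 1.0 − 0.4 = 0.6 points.

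**Cost of keeping everyone.** Suppose non-receivers in one arm get no benefit, so that the effect is 8(1 − f). Power = Φ(effect / (12√(2/54)) − z₁₋α/₂), at alpha 0.05/3:

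| f | Effect | Power, 54 per arm |
|---|---|---|
| 0 | 8.00 | 0.858 |
| 2% | 7.84 | 0.842 |
| 5% | 7.60 | 0.815 |
| 10% | 7.20 | 0.765 |

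For comparison, excluding about 5% (51 per arm) and keeping the full 8-point effect gives 0.835. At 5% non-receipt the price is about 0.02 in power.

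**The case against.** The strongest reply is that the effect may be negligible. One senior anesthesiologist does all blocks under ultrasound, no rate of non-receipt is given, and at the low end of the range the shift is a tenth of a point. Exclusions in two arms would offset each other in part. All of that stands, and it limits the weight of the point.

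A reader might also infer more than the text supports:

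- **That only the block arms lose patients.** PCIA is an assigned component in R and P, so a group P patient without a pump fails the same condition.
- **That the exclusion favours L.** Section 2.8 describes the block after induction and positioning, and PCIA after surgery. Read in that order, intraoperative events threaten receipt of PCIA in R and P more than receipt of the block. A block that cannot be done works the other way. The direction is open.
- **That failed blocks are dropped.** A block injected but ineffective has been received on a plain reading; only one not given counts.
- **That conversions are removed.** "Referral for thoracotomy" is an eligibility criterion in Section 2.3. Section 2.11 does not exclude a converted patient who received the assigned intervention.
- **That the randomized comparison is broken.** It is opened to a bias whose size depends on unknown rates.

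Two further replies stand only in part. The mention of intention-to-treat probably refers to the modified set just defined. That makes it mainly a labelling fault, but the reader is still told that an analysis exists which the section does not contain. And the replacement set proposed below also conditions on later events, namely having the operation and one score. It does, but it no longer conditions on receipt of the allocated treatment, the event most directly tied to the arm.

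**Conclusion.** The point holds in limited form. The primary set selects on receipt of the assigned intervention after open allocation, and no as-allocated analysis regardless of receipt is planned. Nothing in Section 2.11 repairs this: the original-allocation rule acts too late, and the per-protocol set is narrower and shares the selection. With no imputation, excluded patients do not re-enter elsewhere.

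The shift in one arm's mean is about 0.1–3.0 QoR-15 points, if 2–10% of that arm is excluded and those patients would score 5–30 points lower. Neither input comes from the document. The net effect on a comparison may be smaller because of offsetting exclusions, and its sign is not known. This is a cheap improvement, not a defect that invalidates the design.

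**What to change.** In Section 2.11, delete the receipt condition. Define the primary set as all randomized patients who have the operation and at least one QoR-15 score, analysed as allocated whether or not the block or PCIA was given. Keep the present modified set and the per-protocol set as sensitivity analyses, and use one name for the primary set throughout so that the modified intention-to-treat and intention-to-treat labels agree.

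The cost is one rewritten sentence and collecting QoR-15 in non-receivers at the 24, 48 and 72 h visits already in Table 1. The downside is that the estimated effect may be slightly smaller, with the modest loss of power shown above. The change should be made before outcome data are examined, since in an open-label trial a later choice of population would be hard to defend.
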